#### Cardiopulmonary Exercise Testing

The CPET is conducted on an electronically braked cycle ergometer (Ergoline GmbH, Germany) using a ramp protocol according to the statement from the American Heart Association (23, 24). Expired gases are collected and analyzed breath by breath. The test includes several stages (23): (1) rest for 3 min: measurements of rest ECG, blood pressure, heart rate and pulse oxygen saturation; (2) unloading exercise for 3 min; (3) incremental exercise. The increment rate is set between 10 and 20 W·min^−1^ based on patients' characteristics to obtain ~10 min duration. The resistance gradually increases every 6 s. All patients are instructed to cycle with a pedal frequency of 60 revolutions per minute (rpm) and are encouraged to keep exercising until exhaustion or symptoms of chest tightness, chest pain, and shortness of breath, or inability to maintain the pedal frequency of 60 rpm. (4) Recovery: unloading exercise for 3 min, then rest for 5–10 min. The blood pressure is measured by using Tango M2 Stress Test Monitor. The heart rate is determined from the electrocardiogram and expressed as the percentage of the predicted value (220—age). The 12-lead electrocardiogram is continuously recorded during the test. Symptoms are assessed by means of the Borg's Rating of Perceived Exertion (RPE, Borg's 6–20 Scale) (25). Peak exercise is considered the highest VO_2_ achieved during active exercise or early recovery. Heart rate and respiratory exchange ratio (RER) are objective indicators for peak exercise. Peak VO_2_ was determined as the highest mean VO_2_ over 20 s (24). Parameters measured during CPET in our study are listed in Supplementary Table 1. The indications of termination of the test are detailed in Supplementary Table 2. The total exercise time and reason for termination are recorded.

#### Compliance Evaluation

Compliance will be evaluated by counting the number of bottles returned at every follow-up visit (total doses taken divided by total prescribed doses). Of note, the denominator (total prescribed doses) will be calculated over the actual duration when the subject is in the study. Subjects will be informed of the intention to monitor compliance in the informed consent form.

#### Adverse Events and Safety

Adverse events will be assessed and recorded in the case report forms during the whole study. Given the nature of the intervention, the most common adverse reactions related to CDDP including gastrointestinal symptoms, headache, and facial flushing will be monitored. Although CPET is fairly safe with a serious complications rate of <1–5 per 10, 000 tests and a death rate of around 0.5 per 10,000 tests, complications do occur and should be paid attention (24, 26). Major complications include death, myocardial infarction, angina pectoris, arrhythmia, hemodynamic instability, and orthopedic injury (21). Therefore, the test should strictly follow the guideline for exercise stress testing especially the indications to stop the test (Supplementary Table 2).

All serious adverse events (SAEs) will be assessed and reported to the ethics committee in accordance with the International Council for Harmonization of Technical Requirements for Registration of Pharmaceuticals for Human Use Good Clinical Practice (GCP) guidelines (27).

#### Data Management and Monitoring

Data will be collected by trained research staff at each site and recorded in case report forms. This will then be entered into the INCODER database, which is located in the clinical research unit in the Department of Cardiology in the First Affiliated Hospital, Sun Yat-sen University, and supervised by the trial data manager. Data from the INCODER study will be transferred securely to the Research Data Deposit at http://www.researchdata.org.cn/, where it can be accessed and traced securely *via* a specialized administration panel by members of the research team using an encrypted password.

The INCODER study will be overseen by the trial steering committee (TSC) in accordance with the GCP guidance. The TSC, which consists of the chief investigator, study coordinator, site investigators, and statisticians, will independently monitor the process of the study and give advice on the continuation, termination, or amendments of the trial protocol. The study is sponsored by Tasly Pharmaceutical Group Co. Ltd. and will be subject to regular monitoring visits and audits.

#### Patient and Public Involvement

Patients were neither involved in the design or the recruitment and conduct of the study, nor in the assessment of the burden of the intervention. Results will be disseminated to participants on request.

### Statistical Consideration

#### Sample Size Assumptions

This is a superiority study. Sample size calculation is based on the primary outcome of change in total exercise time from baseline to follow-up at 6 weeks. According to the unpublished results of Phase II clinical trial conducted in the United States (16) and our preliminary study (http://www.chictr.org.cn; Registration number: ChiCTR-IIR-17013662), the change of total exercise time is 62.5±19.6 s and 54.5±18.8 s from baseline to week 6 in intensive treatment group and standard treatment group, respectively. We, therefore, assumed the changes of total exercise time as 62.5 s and 54.5 s in the two groups, respectively, and combined standard deviations as 20. The sample size was calculated based on the following formula

$$\begin{array}{l} {\text{N}}_{\text{c}}\;=\;\frac{{\left(Z_{1\;-\;\alpha }\;+\;Z_{1\;-\;\beta }\right)}^{2}\sigma^{2}\left(1\;+\;\frac{1}{r}\right)}{{\left(\mu_{E}\;-\;\mu_{C}-△\right)}^{2}}\\ {\text{N}}_{\text{t}}\;=\;r{\text{N}}_{c} \end{array}$$

where *N*_*c*_ and *N*_t_ denote the sample size of the standard treatment group and the intensive treatment group, respectively. In the equation, σ is the combined standard deviation, and α and β are type I and type II errors, respectively. Here, *r* is the allocation ratio between the two groups, and μ_*E*_ and μ_*C*_ are the average changes of the total exercise time before and after treatment among the intensive treatment group and the standard treatment group, respectively. The superiority margin is Δ. In our study, α = 0.025, β = 0.2, μ_*E*_ − μ_*C*_ = 62.5–54.5 = 8, σ ≈ 20, *r* = 1, and Δ = 0. A sample size of 100 per group will yield 80% power to obtain a significant difference between the 2 groups, using a 2-sample *t*-test at a 1-sided 0.025 level of significance. Considering an ~20% dropout rate, a total of 250 subjects (125 subjects for each group) will be enrolled.

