
Compound Danshen dripping pills (CDDP) or Dantonic, an herbal patent medicine, is widely used in China for the clinical treatment of CAD. CDDP contains three medicinal herbs, *Salvia miltiorrhiza*, notoginseng, and borneol at a ratio of 450:141:8 (15). Its main active pharmacodynamic substances are phenolic acids, saponins, and borneol (16). According to previous studies, CDDP played an important role in the management of CAD through regulating multiple targets that were associated with thrombosis, hyperlipidemia, and vascular remodeling (17). A meta-analysis comprising of 60 randomized controlled clinical trials, including a total of 6,931 patients, showed that CDDP is apparently more effective than isosorbide dinitrate in the treatment of angina pectoris (18). Another systematic review analysis including 34,071 patients with CAD (including patients with angina pectoris and acute myocardial infarction) confirmed the benefits of CDDP in these patients (19). The recommended dose for CAD is 10 pills, three times per day in China (16). In the Phase II clinical trial of CDDP conducted under the supervision of Food and Drug Administration (FDA) in the United States, 125 patients with moderate chronic stable angina pectoris were randomly divided into three groups: placebo, low-, or high-dose group (0, 20, or 30 pills, twice per day, respectively). The results indicated a significant dose-response relationship regarding total exercise duration (TED) following the standard Bruce protocol. After 4 weeks of treatment, the mean improvement of TED compared to placebo was 20 s in the low-dose group (*p* = 0.18) and 43 s in high-dose group (*p* = 0.005). No serious adverse drug reactions (ADRs) were observed (16). Although the changes of TED between low- and high-dose groups were not significantly different, a tendency for better improvement of TED was observed in the higher dose treatment group. For patients with refractory angina with ICR, we found a dose-efficacy tendency when the dose was increased to 20 pills three times per day in clinical practice. Considering more serious conditions, no options or refusal for revascularization, poor response to traditional medical treatment, and different races and nationalities compared with FDA phase II clinical trial, we designed this study and inferred that intensive doses of CDDP would be better for the improvement of exercise capacity in patients with refractory angina without CR.

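### The 80% power rests on an SD of 20 s that the Phase II results quoted in the same article cannot have produced

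*Protocol article*

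**What the plan says.** Under Sample Size Assumptions, the article reports week-6 changes of 62.5±19.6 s (intensive) and 54.5±18.8 s (standard). It gives two sources for them: unpublished results of the US Phase II trial (reference 16) and the group's own preliminary study. From these it "assumed the changes of total exercise time as 62.5 s and 54.5 s in the two groups, respectively, and combined standard deviations as 20". The design values are "In our study, α = 0.025, β = 0.2", equal allocation and zero margin, with a two-sample t-test "at a 1-sided 0.025 level of significance". The conclusion is that "A sample size of 100 per group will yield 80% power to obtain a significant difference between the 2 groups". About 20% dropout raises the total to 250.

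The Background describes the same Phase II trial, also under reference 16. There, "125 patients with moderate chronic stable angina pectoris were randomly divided into three groups": placebo, low dose and high dose. After 4 weeks, "the mean improvement of TED compared to placebo was 20 s in the low-dose group" with p = 0.18; the high-dose figure was 43 s with p = 0.005. It adds that the two dose groups did not differ significantly. It gives no SD and no arm sizes.

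**The concern.** The SD alone fixes the sample size once the 8 s difference is chosen, and required numbers grow with its square. One of the two sources named for the SD is summarised elsewhere in the article in enough detail to recover the variability it must have had. That variability is more than three times the SD used. If the true SD is well above 20 s, the trial has much less than 80% power for the difference it was designed to detect, and a non-significant result would be a likely outcome even if the assumed 8 s benefit were real.

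**Working it through.** **1. The plan's own figure.** Inputs from Sample Size Assumptions: difference 62.5 − 54.5 = 8 s, SD 20 s, one-sided 0.025, power 0.80.

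n per arm = 2 × (1.96 + 0.84)² × 20² / 8² = 98.1, so 99 by the normal formula and 100 with the t-test. Power at 100 per arm is 80.4% (noncentral t). Dropout: 100 / 0.8 = 125 per arm, 250 in total. Everything reproduces.

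**2. The SD implied by the Phase II results.** Inputs from the Background: 125 patients, three arms, 20 s (p = 0.18), 43 s (p = 0.005). Two assumptions are needed that the article does not state: equal arms (m = 125/3 = 41.7) and two-sided p-values.

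SE = difference / t(1 − p/2), and SD = SE / √(2/m), with √(2/41.7) = 0.219.

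- Low dose: 20 / 1.35 = 14.8 s, so SD = 14.8 / 0.219 ≈ 68 s.
- High dose: 43 / 2.87 = 15.0 s, so SD = 15.0 / 0.219 ≈ 68 s.

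**3. The same check in reverse.** With an SD of 20 s the SE would be 20 × 0.219 = 4.4 s. A 20 s difference would then give z = 20 / 4.38 = 4.6, p about 0.000005, where the article reports 0.18. For an SD of 20 s to fit an SE of 15 s, equal arms would need m = 2 × (20/15)² = 3.6 patients each.

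**4. The dose comparison.** The gap between doses is 43 − 20 = 23 s, reported as not significant. Non-significance at two-sided 0.05 needs SE above 23 / 1.98 = 11.6 s, so an SD above 11.6 / 0.219 ≈ 53 s. At SD 20 the gap would give z = 23 / 4.38 = 5.2.

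**5. Sensitivity of the implied SD to what is not stated.**

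| Variant | Implied SD |
|---|---|
| Equal arms, two-sided p | about 68 s |
| 30 to 50 per arm, two-sided p | about 57 to 77 s |
| Split of 20 against 60, two-sided p | about 57 to 58 s |
| p-values Bonferroni-adjusted for two contrasts | about 53 to 64 s |
| One-sided p, equal arms | about 74 to 100 s |

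No variant comes near 20 s.

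**6. What the SD does to the power.** Two-sample t-test, one-sided 0.025, 100 per arm (noncentral t):

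| SD (s) | Power for 8 s | Difference detectable with 80% power |
|---|---|---|
| 20 | 80% | 8 s |
| 30 | 47% | 12 s |
| 40 | 29% | 16 s |
| 50 | 20% | 20 s |
| 68 | 13% | 27 s |

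The last column is close to 2.80 × SD × √(2/100). With all 125 per arm analysed, power for 8 s at SD 68 is 15%. If the Phase II gap of 23 s is used with SD 68, power is 66% at 100 per arm and 76% at 125 per arm.

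**The case against.** The strongest defence is that Phase II does not measure this trial's SD. It used the standard Bruce protocol at 4 weeks in moderate stable angina. This trial uses a cycle ramp set individually to last about 10 minutes, at 6 weeks, in refractory angina with incomplete revascularization. The Discussion says the termination criteria were tightened after the preliminary study. These features could lower the variance by an unknown amount. The 19.6 and 18.8 s may come wholly from the preliminary study, whose data are not shown and so cannot be called wrong. All of this stands.

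It rules out three stronger readings that a reader might draw:

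- That the trial has 13% power. That figure joins the 8 s difference from the sample-size section to an SD from another trial. Keeping to one source at a time gives 80% (8 s, SD 20) or about 66% (23 s, SD 68).
- That the two placebo contrasts are independent confirmations. They share a placebo arm and possibly a pooled variance, so their close agreement adds less than it seems to.
- That 19.6 and 18.8 s are standard errors. Nothing in the article shows this. With an SD of 68 s it would need about (68/19.6)² = 12 patients per arm, a number the article gives nowhere.

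The defence does not rescue the 80%. The article itself names Phase II as a source for the SD. The results it reports from that trial are at 4 weeks for 40 and 60 pills per day, not at week 6 for 30 and 60, so the origin of the input is unclear. Adjustment for baseline and center is unlikely to close the gap: going from 68 to 20 s would need 1 − (20/68)² = 91% of the variance explained, and the Phase II p-values may already be adjusted.

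**Conclusion.** The point holds as a conflict over a sample-size input. It is not an error of arithmetic, since the formula and the dropout inflation both reproduce. The Phase II results in the Background cannot arise from an SD of 20 s: they imply about 68 s with equal arms and two-sided p-values, and roughly 53 to 100 s under plausible alternatives. The conflict itself is firm; the SD that this trial will show is not known from the article. The 80% is therefore unsupported, and it is fragile: an SD of 30 s already brings power for 8 s down to 47%, and 40 s to 29%.

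**What to change.** 1. State which source the 19.6 and 18.8 s come from and whether they are SDs or standard errors, and reconcile them with the Phase II results in the Background.
2. Compute the blinded pooled SD of the week-6 change from patients who have completed, with its confidence limits. The article reports 54 enrolled by December 2021 but not how many had completed. Even with all 54, the 95% limits would run from about 16% below the estimate (√(53/75.0) = 0.84) to 23% above it (√(53/34.8) = 1.23). Pooling across arms hardly inflates the SD: with a true 8 s difference and SD 20 it gives √(20² + 4²) = 20.4 s.
3. Replace the single 80% claim with the power for 8 s and the difference detectable with 80% power over a range of SDs: about 8 s at SD 20, 16 s at SD 40 and 27 s at SD 68.

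The cost is a source check, one blinded calculation and a rewritten paragraph. Because the SD is blinded, no treatment comparison is made. The drawback is that the stated power will probably look less favourable. No change in enrolment is part of this fix, so it corrects the claim without adding power.

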### Statistical Analysis

Statistical analysis will be conducted by the SAS V9.4 software using a two-tailed 0.05 significance level.

Baseline demographic characteristics of the two groups will be presented using descriptive statistics. Continuous variables will be presented with median and interquartile range or mean ± SD. Categorical variables will be expressed as frequencies and percentages. For comparisons between the two groups, *t*-test or rank sum test will be used for continuous variables and the chi-square or Fisher's exact test will be applied for categorical variables.

The primary outcome, changes of total exercise time between the intensive treatment group and the standard treatment group, will be estimated based on the ITT population consisting of all the randomized patients. The general linear model will be used for the primary outcome with covariates of center and baseline exercise time using a 1-sided 0.025 significance level. Data will be presented as mean differences and corresponding *p-*values. Missing data will be imputed by using the last observation carried forward method.

We will further conduct ITT and per-protocol analysis to evaluate the differences in certain secondary outcomes between the two groups. Safety analyses will also be conducted based on a safety set in which all randomized subjects receive ≥1 dose of study medication.

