#### Baseline Visit (Week 0)

Research participants will complete all baseline procedures, including clinical evaluation, angina assessment, SAQ scores, and CPET. Patients who fulfill all the inclusion criteria and none of the exclusion criteria will be randomized with a 1:1 allocation ratio to receive either CDDP 20 pills or 10 pills three times per day. Nitroglycerin will also be dispensed for angina attack when needed. Patients are asked to record every angina attack and nitroglycerin consumption during the study.

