#### Final Evaluation (Week 6)

Final evaluations will be conducted 6 weeks following the baseline assessment. Vital signs, physical examination, 12-lead ECG, angina assessment, SAQ scores, laboratory analyses, and adverse events will be assessed. Blood analyses including CRP, homocysteine, and NT-proBNP for efficacy assessments and other parameters for safety assessments consistent with baseline will be performed. CPET will be conducted for efficacy evaluation.

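### Carrying the last value forward on an endpoint measured only at weeks 0 and 6 scores every missing change as zero, cutting power from 80% to about 40% on the plan's own figures and turning unequal dropout into bias

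*Protocol article*

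**What the plan says.** The primary outcome is the change in total exercise time on cardiopulmonary exercise testing (CPET) from baseline to week 6. The Statistical Analysis section analyses it in all randomised patients, using a general linear model with centre and baseline exercise time as covariates. On missing values it has one rule: "Missing data will be imputed by using the last observation carried forward method".

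The test is done twice. At week 0: "Research participants will complete all baseline procedures, including clinical evaluation, angina assessment, SAQ scores, and CPET". At week 6: "CPET will be conducted for efficacy evaluation". Table 3 marks CPET at V2 and V5 only, the text for weeks 2 and 4 lists none, and no test at early withdrawal is described.

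Under Sample Size Assumptions, the authors "assumed the changes of total exercise time as 62.5 s and 54.5 s in the two groups" and took "combined standard deviations as 20". For a two-sample t-test with one-sided α = 0.025 they conclude: "A sample size of 100 per group will yield 80% power to obtain a significant difference between the 2 groups". They then allow for losses: "Considering an ~20% dropout rate, a total of 250 subjects (125 subjects for each group) will be enrolled".

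**The concern.** Carrying a value forward presupposes an on-treatment value to carry. Here the only earlier value is the pre-randomisation baseline, so the rule amounts to imputing no change for anyone without a week-6 test.

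That conflicts with the plan's own expectations. Both arms receive active drug and both are expected to gain close to 60 s, about three times the planning SD. Imputed zeros would form a separate cluster far below the observed changes. They pull the treatment difference towards zero and inflate its variance.

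The sample size and the analysis also treat dropouts differently. Raising 100 to 125 per arm treats dropouts as lost and leaves 100 observed patients per arm with the full 8 s effect. The analysis instead keeps all 125 per arm, about 25 of them with an artificial zero. At stake are the power of the only primary comparison and, if dropout differs between arms, the validity of its estimate and p-value.

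**Working it through.** **Inputs** (Sample Size Assumptions, unless noted): mean changes 62.5 s (intensive) and 54.5 s (standard); SD 20 s; one-sided α = 0.025; power 80%; margin 0; 1:1 allocation; dropout about 20%; 125 enrolled per arm. CPET at weeks 0 and 6 only (Table 3).

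**1. The plan's own figure.**
- n per arm = 2 × 20² × (1.960 + 0.842)² / 8² = 98.1, so 99; the plan states 100.
- Power at 100 per arm: SE = 20 × √(2/100) = 2.83 s; Φ(8/2.83 − 1.96) = 80.7% (80.4% by the noncentral t).
- 100 / 0.8 = 125 per arm.

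The plan's arithmetic reproduces, for an analysis of 100 completers per arm.

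**2. The same trial under the stated missing-data rule.** Let q be the fraction without a week-6 test, unrelated to outcome. Each arm is a mixture of zeros and observed changes:
- mean = (1 − q)μ
- variance = (1 − q)σ² + q(1 − q)μ²

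With q = 0.2 in both arms:
- Difference: 0.8 × 62.5 − 0.8 × 54.5 = 50.0 − 43.6 = 6.4 s.
- Variance, intensive: 320 + 0.16 × 62.5² = 945 (SD 30.7 s).
- Variance, standard: 320 + 0.16 × 54.5² = 795 (SD 28.2 s).
- Average SD: √((945 + 795)/2) = 29.5 s.
- SE: √((945 + 795)/125) = 3.73 s.
- Power: Φ(6.4/3.73 − 1.96) = 40%.

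Simulating the planned linear model with seven centres and baseline exercise time gave 39–41%, so covariate adjustment does not recover the loss. Restoring 80% power under this rule would take (1.960 + 0.842)² × (945 + 795) / 6.4² ≈ 334 per arm.

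| Missing, both arms | Power, zeros imputed (n = 125) | Power, observed patients only |
|---|---|---|
| 5% | 73% | 87% |
| 10% | 59% | 85% |
| 15% | 49% | 83% |
| 20% | 40% | 81% |
| 25% | 34% | 78% |

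**3. Unequal dropout.** The article gives no rates by arm, so the splits below are assumptions, chosen to average 20%.

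*No true difference (both arms gain 58.5 s):*
- 15% missing (intensive) versus 25% (standard): spurious difference (0.85 − 0.75) × 58.5 = +5.85 s; SE = √((776 + 942)/125) = 3.71 s; one-sided rejection Φ(5.85/3.71 − 1.96) = 35% (32% in simulation of the linear model). Analysing observed patients under the same dropout gave 2.3%.
- 18% versus 22%: spurious difference 0.04 × 58.5 = +2.3 s; rejection rate about 9%.

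*True difference 8 s:*
- 25% (intensive) versus 15% (standard): 0.75 × 62.5 − 0.85 × 54.5 = 0.55 s; power about 3.5%.
- 15% versus 25%: 0.85 × 62.5 − 0.75 × 54.5 = 12.25 s, an overstatement.

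Each percentage point of imbalance moves the estimate by about 0.01 × 58.5 ≈ 0.6 s. Starting from 6.4 s at an average of 20% missing, a gap of 6.4 / 58.5 ≈ 11 points removes the effect.

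**The case against.** **The power loss depends on SD = 20.** This is the strongest objection. The Background reports, for an earlier trial of 125 patients in three groups, gains over placebo of 43 s (p = 0.005) and 20 s (p = 0.18). Assuming about 42 per group and simple two-sample tests, SD = difference / (t × √(2/n)) gives about 68 s from both results. That trial used a treadmill at 4 weeks, so transfer to this setting is uncertain. At SD 40, power with 20% missing is 22% under the rule against 29% for completers; at SD 70 it is 11% against 12%. With a larger SD, then, the rule costs less power, but the trial is far below 80% power anyway. The bias remains: the spurious 5.85 s does not depend on the SD, and the false-positive rate in the 15%/25% case is still about 10% at SD 70.

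**The 20% is an allowance, not a forecast.** True. The loss is smaller with fewer missing tests, as the table shows, but at 10% missing power is still 59%.

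**Nothing in the article points to a 10-point gap in dropout.** Also true. Both arms take 20 blinded pills per dose for six weeks, and adverse reactions are described as mostly mild. With equal dropout the type I error stays near nominal (2.9% simulated), and the rule then attenuates the estimate, which is conservative for a superiority claim. But the arms differ twofold in active dose, and even a 4-point gap raises the error rate to about 9% on the plan's figures.

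**The full protocol may include a test at early withdrawal.** Some patients would then carry that value forward instead of baseline. The article describes none, and patients with no further test would still be scored zero.

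**Conclusion.** The rule is wrong as written and should be changed before the data are analysed. That missing changes become zero follows directly from the visit schedule and the missing-data rule, and is secure on the text shown. On the plan's own figures, with the full 20% missing equally in both arms and unrelated to outcome, power is about 40% instead of 80% because the difference shrinks and its SD grows by nearly half. The size of this loss depends on SD 20 and on the missing fraction. Bias away from the null needs unequal dropout; the splits used to illustrate it are hypothetical, but the sensitivity of about 0.6 s per percentage point is not, given the planned gains.

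**What to change.** - Drop last observation carried forward for the primary endpoint.
- State that the week-6 CPET will be sought from every randomised patient, including those who have stopped study drug.
- Fit the planned general linear model after multiple imputation within arm, using baseline exercise time, centre, and the week-2 and week-4 Seattle Angina Questionnaire scores, CCS class and angina counts already collected.
- Keep zero-change imputation as a sensitivity analysis, together with a delta-adjusted tipping-point analysis, and report missing week-6 tests by arm.
- Optionally, for the secondary outcomes recorded at weeks 2, 4 and 6, use a repeated-measures model. This is separate from the primary defect.

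The cost is new wording in the statistical section and modest programming. The week-6 visit already exists, so no visits are added. If patients who stop study drug are not currently followed to week 6, continuing to test them changes trial conduct and would need an amendment approved by the ethics committee. Recruitment had reached 54 of 250 in December 2021, so patients already enrolled may be affected.
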